**Figure 1 F1:**
[figure not shown]
Flowchart of the study design. PA, prism adaptation. EMT, eye movement training.

**Table 1 T1:** Schedule of enrollments, interventions, and assessments.

		**Screening**	**Randomization**	**Intervention**	**Follow up**
**Time point**		**Within one weeks**	**Day 0**	**2 weeks** **(10 sessions)**	**Post-2 weeks**
			**T** _0_	**T** _1_	**T** _2_
Enrollments	Informed consent	√			
	Demographic characteristics	√			
	Medical history	√			
	Eligibility assessment	√			
	Radom allocation		√		
Intervention	Conventional rehabilitation			√	
	PA			√	
	EMT			√	
	PA & EMT			√	
Assessment	Cognitive level (MMSE)	√		√	
	Behavioral inattention test-conventional subset			√	√
	Catherine bergego scale			√	√
	Modified barthel index			√	√

PA, prism adaptation; EMT, eye movement training; MMSE, Mini-mental State Examination.

### 2.2. Consent and eligibility

Potential participants will be primarily screened and those who meet inclusion and exclusion criteria will be invited to participate in this study. All subjects will have an informed consent form signed by themselves or a legal representative prior to undergoing any study procedures. The inclusion and exclusion criteria for selecting participants are listed as follows.

#### 2.2.1. Inclusion criteria

a) Adult patients older than 18 and younger than 80 years.b) First stroke with ischemic or hemorrhagic brain injury on CT and MRI.c) The subacute phase of stroke: Duration 1 to 12 weeks after stroke onset.d) Diagnosis and confirmation of USN: a pathological performance on one subtest of the Behavioral Inattention Test-Conventional Subset (BIT-C).e) The patient can sit in a stable position.f) Complete vision or normal after correction.g) The patient is right-handed.

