## 1. Introduction

Stroke is the second cause of death and the leading cause of disability worldwide (1). Poststroke patients usually suffer from multiple dysfunctions and complications that affect their health-related quality of life (2). Unilateral spatial neglect (USN) is a frequent and disabling condition after stroke, affecting approximately 30% of acute and subacute stroke survivors (3). USN is mainly related to damage to neural networks associated with spatial information processing and attentional control (4) and is defined as the inability to orient, detect, or respond to relevant stimuli in the visual field opposite to the brain lesion and unrelated to sensory and motor dysfunction (5). In clinical, approximately 40% of patients with USN are consistently affected by neglect symptoms (6). Compared to other stroke survivors, patients with USN are associated with poorer rehabilitation outcomes of other stroke symptoms (7) and longer hospital stays (8, 9). In addition, USN increases the consumption of health resources and adds to the burden on families (10, 11).

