### 2.5. Randomization and blinding

A random number list is generated by a computer and consists of 88 random numbers. The random numbers were arranged from the smallest to the largest to obtain the serial number R. It is stipulated that group A (PA) with *R* = 1–22, group B (EMT) with *R* = 23–44, group C (PA & EMT) with *R* = 45–66, and group *D* (control) with R = 67–88. The resulting sequence of random assignments was placed in sequentially coded, sealed, impermeable envelopes. The investigator in charge of recruitment opens the envelope according to the order of patient enrollment and assigns the subjects to the appropriate subject group.

This study is a single-blind design, and only the investigator conducting the assessment is blinded to group assignment. The therapist cannot be blinded due to using the supervised intervention. In addition, blinding of subjects is not feasible due to the difference in intervention methods. All outcome assessments for this study will be conducted by a separate professional therapist who is not involved in any other part of the study. Moreover, participants will be unblinded when any clinical situation associated with adverse events or patient withdrawal occurs.

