### 2.7. Baseline data

Baseline data are collected after informed consent and before randomization. The baseline assessment includes demographic characteristics such as sex, age, time of onset, cause of damage, and assessment scales including the Mini-Mental State Examination, Catherine Bergego Scale, Behavioral Inattention Test-Conventional Subset (BIT-C), and Modified Barthel Index (MBI). All baseline data will be collected *via* paper forms.

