### 2.12. Data analysis

IBM SPSS Statistics for Windows, Version 26.0 (IBM Corp., Armonk, NY, United States) will be used for statistical analysis. 2-tailed *P* < 0.05 will be considered a statistically significant difference. Continuous variables will be expressed as mean with standard deviation or median with interquartile range, whereas categorical data will be expressed as counts and percentages. Baseline comparisons will be used to examine potential differences between 4 groups. Age, time of onset, and MMSE will be analyzed by ANOVA or Kruskal-Wallis test. Sex, cause of damage will be measured using Chi-square tests. The Kolmogorov-Smirnov test will be used to evaluate the normality of distributions. If a normal distribution is confirmed, one-way ANOVA will be used to examine the effectiveness of intervention between the 4 groups at T1, T2, with Bonferroni correction for multiple comparisons as a *post hoc* test. Otherwise, Kruskal-Wallis (non-parametric test) will be used.

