Since patients with USN themselves suffer from attention deficits and other cognitive dysfunctions, an unreasonable combination of therapies rather leads to an aggravation of neglect symptoms (48), and therefore, the selection of the combination of different interventions needs to take into account the relevant influencing factors and the patient's tolerance. Saevarsson et al. (19) and Choi et al. (20) combined an active engagement (PA) with a passively received (neck vibration or FES) intervention, both of which showed better efficacy of the combined intervention, but both interventions used in our trial required patients to actively participate, so this may be a limitation of this interventional approach. However, the few patients who completed the intervention described that they were able to accept the intensity of the training and did not experience any particular fatigue or difficulty accomplishing it.

There are other limitations to our study. (a) Our target population was set to patients with subacute stroke, and the efficacy of patients in the chronic phase was not discussed. (b) The efficacy of interventions with active engagement is influenced by cognitive level, and we only mentioned the ability to cooperate with the therapist in the eligibility criteria, discussed the overall efficacy, and did not stratify the analysis of the efficacy of patients with different cognitive levels. (c) Patients with severe USN were excluded from the study, so the efficacy for this group is not yet clear. (d) This is a preliminary exploratory study, and the follow-up time in this trial is only 2 weeks after the end of treatment.

We aimed to conduct a randomized controlled trial to investigate whether the PA combined with EMT has the potential to be a promising treatment option for poststroke USN. If this study provides positive results, it will be possible to recommend that these techniques be implemented in treatment protocols for patients with USN.

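### Time since stroke (1 to 12 weeks at entry) is recorded before randomisation but left out of the outcome analysis, which costs precision and protection against chance imbalance, not validity

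*Protocol article*

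**What the plan says.** Protocol article, section 2.2.1, admits patients over a wide window: "The subacute phase of stroke: Duration 1 to 12 weeks after stroke onset". Section 2.7 lists what is collected before randomisation, including "demographic characteristics such as sex, age, time of onset, cause of damage".

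Section 2.5 describes allocation: "A random number list is generated by a computer and consists of 88 random numbers". The numbers are ranked and cut into four groups of 22. No stratification factor is named, and "The investigator in charge of recruitment opens the envelope according to the order of patient enrollment".

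Section 2.12 gives time of onset one role, a comparison between groups at baseline: "Age, time of onset, and MMSE will be analyzed by ANOVA or Kruskal-Wallis test". It does not say what follows if that test is significant. For the outcomes, "one-way ANOVA will be used to examine the effectiveness of intervention between the 4 groups at T1, T2", with Bonferroni-corrected post hoc comparisons, or Kruskal-Wallis if normality is not confirmed. Neither test contains a covariate.

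**The concern.** A patient at week 1 and a patient at week 12 with the same BIT-C score may well differ in how much they will improve over the next 2 to 4 weeks, whatever the treatment. If so, time since stroke is prognostic. Leaving it out has two effects: its contribution stays in the error term, and an accidental difference in mean onset between arms goes uncorrected in the estimate. With about 20 patients analysed per arm, such differences are not rare.

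The baseline test does not help. A non-significant result does not show that an imbalance is harmless, and a significant one leads to no stated action. The variable is already in the data set, so the plan gives up a gain that needs no extra patients or visits. Because section 2.12 names the outcome test, this is a choice the protocol has made and not a detail left to an unseen analysis plan.

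**Working it through.** **Inputs from section 2.4.** BIT-C change in the pilot: combined 39.33 (SD 18.717), eye-movement training (EMT) 26.33 (SD 7.638), prism adaptation (PA) 20 (SD 2.828). Alpha is 0.05 (two-sided by section 2.12), beta is 0.2, dropout is 10%, with 22 per group.

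**Step 1: the plan's own figure.** Two-sample t-test, noncentral t.
- Combined vs EMT: difference 13.00, SD = √((18.717² + 7.638²)/2) = 14.29. This gives 20 per group.
- Combined vs PA: difference 19.33, SD = √((18.717² + 2.828²)/2) = 13.39. This gives 9 per group.
- 20 × 1.1 = 22 per group, 88 in total.

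Both stated sizes are reproduced, and neither depends on time since stroke.

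**Step 2: is the unadjusted test valid?** Four-arm trials were simulated (20,000 runs, 20 per group, no true effect, onset prognostic but omitted). Type I error was 5.1% when onset explained 20% of the variance and 4.8% when it explained 50%. The mean difference between arms was 0. The test is valid.

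**Step 3: how large is chance imbalance?** The onset distribution is not in the documents, so two are assumed. SE of the difference in mean onset = SD × √(2/n).

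| Assumed onset | SD (weeks) | n per arm | SE (weeks) | Differ by more than 1 week |
|---|---|---|---|---|
| Uniform, 1–12 weeks (11/√12) | 3.18 | 20 | 1.00 | 32% |
| Uniform, 1–12 weeks | 3.18 | 22 | 0.96 | 30% |
| Mostly early | 2.34 | 20 | 0.74 | 18% |
| Mostly early | 2.34 | 22 | 0.71 | 16% |

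The percentages are for one given pair of arms. The early-enrolment case is 1 + 11 × Beta(1, 2.5).

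**Step 4: what would adjustment gain?** The share of variance explained (R²) is also an assumption. The unadjusted SE at 20 per group is 14.29 × √(2/20) = 4.52 points. Adjustment multiplies it by √(1 − R²). The noncentrality is 13 divided by the result. The loss of a few degrees of freedom is ignored. The implied slope is √R² × 14.29/3.18 points per week (uniform onset).

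| R² | Slope | Adjusted SE | Noncentrality | Power, n = 20 | n per group for 80% |
|---|---|---|---|---|---|
| 0 | 0 | 4.52 | 2.88 | 80% | 20 |
| 0.05 | 1.0 | 4.41 | 2.95 | 82% | 20 |
| 0.10 | 1.4 | 4.29 | 3.03 | 84% | 19 |
| 0.20 | 2.0 | 4.04 | 3.22 | 88% | 17 |

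At R² = 0.20, a 1-week imbalance shifts a contrast by about 2 points, against a planned difference of 13.

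**Step 5: an upper limit from the pilot.** With a slope common to all arms, the onset-driven SD cannot exceed the total SD of any arm. The EMT arm then gives R² ≤ 7.638²/14.29² = 58.3/204.3 = 0.29, a slope of at most 7.638/3.18 = 2.4 points per week. The PA arm gives R² ≤ 2.828²/14.29² = 0.04, a slope of at most 0.9.

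**The case against.** A reader might infer that differences in spontaneous recovery are confounded with the treatment effect. The documents do not support that. All four arms, control included, are randomised and run concurrently, so onset is balanced in expectation. The chance shift is already part of the standard error and the p-value, as step 2 shows.

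A reader might also take the Introduction's statement that "approximately 40% of patients with USN are consistently affected by neglect symptoms" to mean that the other 60% recover by themselves during weeks 1 to 12. The sentence gives no time frame, does not say that the rest recover without treatment, and does not place recovery inside the entry window. It is indirect support at most. That onset is prognostic here is plausible, but it is not a figure the protocol supplies.

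The size is open to challenge too. The PA arm's pilot SD would allow R² of only about 4%, where adjustment gains roughly 2 points of power. The three pilot SDs differ so much (2.8 to 18.7) that none is a firm limit, but they rule against large claims: a slope of 3 points per week implies an onset-driven SD of 9.5, more than the whole EMT SD.

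On cognition, the Discussion says "The efficacy of interventions with active engagement is influenced by cognitive level" and lists the absence of an analysis by cognitive level as a limitation. That concerns a treatment effect that varies with MMSE. An MMSE main effect in the model would not address it, so it is no argument for adjustment beyond precision.

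Finally, adjusting for a prognostic covariate is an efficiency choice, and no passage is contradicted. That is fair. What stands is that the plan gives a baseline variable it already holds a use that achieves nothing and omits it where it could help.

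**Conclusion.** The point holds as one of precision and chance imbalance. The unadjusted comparison is unbiased with type I error near 5%, and the sample size calculation is unaffected. Two given arms will differ by more than a week in mean onset in roughly 16% to 32% of trials, depending on the assumed onset distribution and on 20 or 22 per arm. Adjustment would lift power for the 13-point combined vs EMT contrast from 80% to about 82%, 84% or 88% if onset explains 5%, 10% or 20% of the variance of BIT-C change. More than about 29% is implausible against the EMT pilot SD.

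These figures assume a linear onset effect common to all arms and an SD of 14.29. The R² applies to change scores, whereas section 2.12 does not say whether change or the score itself is compared. Once the baseline score is in the model, the relevant R² is what onset adds to it, which the documents cannot show. The gain is modest and uncertain, but it costs almost nothing.

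**What to change.** In section 2.12, replace the unadjusted outcome ANOVA by a prespecified ANCOVA for BIT-C, CBS and MBI at T1 and at T2, with group as the factor and two covariates: the baseline value of that outcome and weeks since stroke. Baseline MMSE may be added, for precision only. Report this model whatever the baseline comparisons show, and apply the Bonferroni correction to its adjusted group differences.

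Kruskal-Wallis takes no covariates, so replace that branch as well: if residuals are clearly non-normal, use a rank-based or robust version of the same model.

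Keep the baseline table as description and drop its significance tests as a guide to adjustment. Leave the randomisation list unchanged, since recruitment is under way. Fix the covariates before results are seen, or the adjustment will look selective.

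The cost is two or three of the 76 residual degrees of freedom (80 patients analysed minus 4 groups) and slightly more analysis work. There are no new data, visits or patients.

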#### 2.2.2. Exclusion criteria

a) Severe cognitive impairment (MMSE <16) and non-cooperation.b) Severe USN (star cancellation tests <8).c) Severe non-spatial attention deficit (digital checking method).d) Patients with severe organ diseases.e) Inability to comply with the time frame of this study.f) Unsigned informed consent.

All subjects will sign an informed consent document before undergoing any study procedures.

### 2.3. Sample and recruitment

Patients with USN in the subacute phase of stroke will be recruited from 2 November 2021 to 1 June 2023 at the Second Clinical Medical College of North Sichuan Medical University. Recruited participants will be required to meet the USN diagnostic criteria, including nurse or family member reports of disproportionate orientation toward the impaired side, and <52 stars were removed from the cancellation test. Patients will be initially screened through a case system or clinician notification and will be carefully evaluated for meeting eligibility criteria once they have signed an informed consent form.

### 2.4. Sample size estimation

In the preexperiment, the changes in BIT-C scores before and after the intervention were 39.33 ± 18.717 for the combined intervention group, 26.33 ± 7.638 for the eye-movement training group, and 20 ± 2.828 for the PA training group. Using the PASS software, the probability α of occurrence of the Type I error was set to 0.05, the probability β of occurrence of the Type II error was calculated as 0.2, the calculation results showed that the combined intervention and eye-movement training groups required 20 samples each, and 9 samples were required for each of the combined intervention and PA training groups. Therefore, taking into account a 10% sample dropout rate, the total sample size was finally determined to be 88 cases, with 22 cases in each group.

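### The stated 80% power is for single pairs at unadjusted two-sided 0.05, but the planned pairwise tests are Bonferroni-corrected across four arms, so it does not apply to combined versus EMT

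*Protocol article*

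**What the plan says.** Section 2.4 takes pilot BIT-C changes of "39.33 ± 18.717 for the combined intervention group" and "26.33 ± 7.638 for the eye-movement training group", and 20 (SD 2.828) for PA. On error rates it says that "the probability α of occurrence of the Type I error was set to 0.05" and "the probability β of occurrence of the Type II error was calculated as 0.2". Two pairs are then sized separately: for the first, "the combined intervention and eye-movement training groups required 20 samples each"; for combined versus PA the figure is 9 per group. The larger number is carried forward: "taking into account a 10% sample dropout rate, the total sample size was finally determined to be 88 cases, with 22 cases in each group".

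Section 2.12 sets the significance rule: "2-tailed *P* < 0.05 will be considered a statistically significant difference". If normality is confirmed, the four groups are compared by one-way ANOVA at T1 and T2, with post hoc pairs tested "with Bonferroni correction for multiple comparisons". Otherwise Kruskal-Wallis is used. The number of corrected comparisons is not given.

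Section 2.10 removes dropouts from the efficacy analysis, so attrition reduces the analysed sample directly.

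**The concern.** Sections 2.4 and 2.12 describe two different tests of the same contrast. One is a single comparison at 0.05; the other is one of several comparisons sharing 0.05. Nothing in section 2.4 carries the correction into the sample size, and 20 per arm is the smallest number that reaches 80% without it, so there is no slack to absorb it.

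The contrast affected is the one that matters most. The Introduction hypothesises that the combination does better than its components, and combined versus EMT is the pair that set the sample size. If the assumed 13-point difference is real, the planned test has a materially larger chance of missing it than the stated 20%. A non-significant result could then be read as showing that combining adds nothing to EMT.

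**Working it through.** **Inputs (section 2.4).** Combined 39.33, SD 18.717; EMT 26.33, SD 7.638; PA 20, SD 2.828. Alpha 0.05, two-tailed (section 2.12); power 0.80; 10% dropout; 22 per arm.

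**Step 1: reproduce the plan's figures.** Two-sample t-test, noncentral t, with SD = √((s₁² + s₂²)/2).

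- Combined vs EMT: difference 39.33 − 26.33 = 13.00; SD = √((18.717² + 7.638²)/2) = 14.29; d = 13.00/14.29 = 0.909. At two-sided 0.05, n = 20 gives 80.0% power.
- Combined vs PA: difference 39.33 − 20 = 19.33; SD = √((18.717² + 2.828²)/2) = 13.39; d = 19.33/13.39 = 1.444. At two-sided 0.05, n = 9 gives 82.0% power.

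Both match the protocol exactly. Other variants do not: for combined vs EMT and combined vs PA, the normal approximation gives 19 and 8, Welch 21 and 10, and one-sided 16 and 7.

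**Step 2: evaluable patients.** 22 × 0.9 = 19.8 per arm. The 22 is 20 × 1.1; dividing instead, 20/0.9 = 22.2, gives 23. At unadjusted 0.05, power is 79.6% with 19.8 and 80.0% with 20.

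**Step 3: apply the correction, same two-arm formula, 19.8 per arm, combined vs EMT.**

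| Comparisons corrected | Alpha per pair | Power |
|---|---|---|
| 1 (as sized) | 0.05 | 79.6% |
| 2 | 0.025 | 70.0% |
| 3 | 0.0167 | 64.0% |
| 6 (all pairs of four arms) | 0.0083 | 53.6% |

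For six pairs, power is 51% at 19 per arm, 54.2% at 20, and 60.0% at 22 with no dropout; Welch gives 50.9% at 19.8. Reaching 80% would take 32 evaluable per arm. Combined vs PA keeps 95.5% at 19.8 and 95.7% at 20.

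**Step 4: pooled four-group error term.** A post hoc test after ANOVA usually takes its error from all four arms. That needs a control SD, which the article does not give, so three values are assumed. Simulation with 20 per arm and alpha 0.05/6, combined vs EMT:

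| Assumed control SD | Pooled SD (pair's own: 14.29) | Rejection, true difference 13 | Rejection, true difference 0 (nominal 0.83%) |
|---|---|---|---|
| 2.828 | 10.30 | 82% | about 6% |
| 7.638 | 10.90 | 79% | about 4.7% |
| 18.717 | 13.85 | 60% | about 1.2% |

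The pooled SD averages in low-variance arms and so understates the standard error for this pair. The gain in rejection is bought with false positives.

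**Step 5: the fixed-sequence alternative.** Simulated probability that both combined vs PA and combined vs EMT succeed, each at two-sided 0.05: 78% at 19 per arm and 80% at 20 with equal-variance tests; 77% and 79% with Welch tests.

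**The case against.** The strongest objection is that 54% is not the power of the planned test. A Bonferroni post hoc after ANOVA normally uses the pooled error term, which gives 60–82% across the assumed control SDs, all above 54%. This stands as a reason not to present 54% as the single answer. It does not rescue the 80%: rejection comes close to that level only where the test rejects a true null for this pair at roughly six times the nominal rate or more.

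Second, six comparisons is an inference. Section 2.12 gives no count, and section 2.4 sizes only two pairs. This also stands, and is why the range is shown. But correcting for even two comparisons gives 70% on the two-arm basis.

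Third, the omnibus ANOVA comes first, and Bonferroni applies only on the normality branch. True, but a significant omnibus test does not show that the combination beats EMT, and the non-parametric branch has no stated power.

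Fourth, the Discussion calls the study preliminary and exploratory, and the inputs are pilot estimates, so two-digit power figures should not be over-read. That lowers the stakes, but the same Discussion foresees recommending the techniques if results are positive.

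A reader might also infer that the dropout arithmetic leaves the trial underpowered. It does not: the slip costs 0.4 percentage points.

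**Conclusion.** The point holds. The 80% in section 2.4 belongs to an uncorrected two-arm test that section 2.12 does not plan. On the protocol's own means, SDs and two-arm basis, with about 20 evaluable per arm, power for combined versus EMT is about 54% for six corrected pairs, 64% for three and 70% for two. With the pooled ANOVA error, nominal rejection is about 60–82% as the assumed control SD falls from 18.7 to 2.8, with a type I error for this pair of up to about 6% against 0.83%. Combined versus PA is unaffected in practice, at about 96%.

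A reader might conclude that the key comparison simply has 54% power. That is too firm, because it fixes both a comparison count and an error term that the article does not state. Nor does it follow that the trial must grow to 32 evaluable per arm; a different testing order avoids that. All figures treat one scale at one visit. The protocol has two primary scales (BIT-C and CBS) and tests at T1 and T2, and correcting for those as well would lower power further.

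**What to change.** Keep 88 patients and choose one of two routes before outcome data are analysed.

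1. **Keep Bonferroni.** State in section 2.12 how many comparisons are corrected, and restate in section 2.4 the power for combined versus EMT at that alpha (about 54% for six pairs on the two-arm basis).
2. **Prespecify a fixed sequence** for BIT-C change, the quantity that was sized, at one named visit: combined versus PA, then combined versus EMT, each at two-sided 0.05 with an unequal-variance test. Claim that the combination is superior to both components only if both succeed. Confine Bonferroni to the other four pairs, and treat CBS and the other visit as supportive. Joint power is about 77–79% at 19–20 per arm (78–80% with equal-variance tests).

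Under either route, amend the dropout sentence to say that 22 per arm leaves about 19–20 evaluable.

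The cost is wording in sections 2.4 and 2.12, with no extra patients. Route 2 has a real downside: comparisons with control become exploratory or move later in the sequence. Route 1 leaves the testing plan as it is but requires accepting, and stating, lower power for the main contrast.
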